#### Collaborative analysis

The descriptive data will be triangulated against interviewer field journals, then thematically analysed to provide more in-depth information on the content and face validity of the statements. We will also use this method to inform the recommended age of suitability for self-complete by children. We will engage the CWG using Collaborative Yarning to seek guidance before finalisation of the items and the determination of whether age-relevant versions of the measure are warranted.

### Phase 3: Co-design of culturally responsive pictorial elements

In Phase 3, we will use co-design methods to create Aboriginal and Torres Strait Islander artwork to accompany each well-being item developed in Phase 2. The artwork will be taken back to communities for feedback and refinement, to ensure it reflects shared cultural themes while incorporating the diverse perspectives gathered through the co-design workshops. This process will ensure the measure is visually accessible, culturally grounded and meaningful to Aboriginal and Torres Strait Islander children from diverse communities and language groups.

#### Knowledge holder recruitment

We will recruit approximately 15–20 Aboriginal and Torres Strait Islander children from each of the diverse communities participating in the co-design workshops (informed by Phase 2b findings regarding appropriate age groups). An Aboriginal and Torres Strait Islander artist with experience across diverse communities will be engaged to lead the artwork development. The artist will be identified through consultation with partner organisations, prioritising those with experience working with children, creating culturally appropriate educational materials and who hold cultural authority to create artwork that resonates across diverse Aboriginal and Torres Strait Islander communities.

#### Co-design process

Using Art and Yarning methods established in Phase 2, we will facilitate collaborative co-design workshops in diverse communities where children work with the artist to explore visual representations for each well-being item. Children will be presented with the finalised well-being items from Phase 2, and yarning circles will be used to explore how children visualise and conceptualise each well-being component. Children will be engaged in creating initial sketches and artwork concepts that reflect their cultural knowledge, stories and artistic traditions. The artist will then synthesise ideas from across all community workshops to develop a unified artwork version that incorporates shared cultural themes and diverse perspectives. The artist will return to participating communities to present the draft artwork and gather feedback, refining the designs through iterative consultation with children, local elders (where appropriate) and the CWG to ensure the final artwork reflects cultural knowledge that resonates across diverse communities. The co-design workshops will take place over 1–2 weeks within each community, followed by community feedback sessions. Children will receive art materials packs, and artists will be appropriately remunerated for their time, expertise and cultural knowledge.

#### Cultural authority and protocols

Throughout the artwork development process, we will ensure appropriate cultural protocols are followed. This includes seeking guidance from elders and cultural knowledge holders within each community, and ensuring artists have the cultural authority to create and share visual representations. We will respect intellectual property rights and cultural ownership of designs, and follow appropriate processes for depicting cultural symbols, stories and knowledge. Necessary permissions for use of cultural imagery and designs will be obtained in accordance with community protocols and cultural governance processes.

#### Collaborative analysis and refinement

Each community and the CWG will have the opportunity to review all artwork concepts to ensure cultural appropriateness, authenticity and alignment with the well-being items. Children from each community will be engaged in final review sessions to provide feedback on which visual representations best capture the meaning of each item within their cultural context.

#### Collaborative analysis

At critical points during the artwork co-design and feedback process, the CWG will be convened to inform the iterative development of the unified artwork version and to ensure the final measure appropriately celebrates and represents Aboriginal and Torres Strait Islander peoples from diverse cultural groups across Australia.

### Phase 4: Develop and validate the pictorially-supported descriptive system

In Phase 4, guided by the CWG, we will build on best practice measure development approaches to incorporate validation of items with accompanying pictures to test the draft illustrated well-being items (developed in Phases 2 and 3) and develop the descriptive system for the measure. This phase will use quantitative methods to validate the measure through children experiencing it in practice, with the artwork accompanying all items.

#### Knowledge holders, recruitment and data collection

The items developed in Phases 2 and 3 will be included in an online survey for Aboriginal and Torres Strait Islander children living in metropolitan, rural and remote areas. A sample of around 300 children will be recruited via partner organisations and through investigator and research team networks. A purposive sampling approach will be used to ensure diversity across age, sex and remoteness. The online survey will take around 30 min to complete. Children will enter a prize draw to win an art materials pack; a general approach that has been used successfully in our existing project with youth (NHMRC GNT1125434). This sample size will be sufficient to conduct psychometric analyses, based on our experience and our existing project with youth^23^ and adults,^24^ in which a similar sample size completed a survey with 30 candidate well-being items.

#### Statistical analysis

We will conduct classical psychometric analysis at the item and dimension level to assess reliability and validity. We will also explore differences across sociodemographic groups. Factor analysis will be undertaken to ensure the final measure includes a broad set of dimensions of well-being relevant to Aboriginal and Torres Strait Islander children. Exploratory Factor Analysis will initially be used to examine dimensionality of groups of well-being items, without imposing a pre-specified structure of dimensions. Items that do not load on any factor will be considered for exclusion from the measure alongside other criteria to ensure that crucial items (eg, identified as important in Phase 2) are not excluded. Confirmatory Factor Analysis will also be used to test the preferred dimension structure. A range of statistics will be used to assess model fit and guide dimension development. We will also use Item Response Theory methods to understand measurement characteristics of the items (including measurement discrimination and differential item functioning) and inform decision making about which items are included in the final measure.^12^

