#### Sample size

The optimal sample size for a BWS survey is dependent on the final number of well-being items and response levels to be included in the descriptive system.^56^ Based on our previous measure development, we anticipate that there will be 16–18 items in the final measure. It is not feasible to present all combinations of well-being items to all children, therefore we will use a balanced incomplete block design.^57^ Given large sample properties can be achieved with around 50 respondents per block or version,^27 29 55 58^ a design with 8 blocks and around 50 respondents/block (n~400) will be robust enough to estimate main effects, first order interactions and examine differences between subgroups. This sample size is also consistent with previous successful applications of this method.^2729 58^,^61^

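### Phase 4 builds and tests the factor structure in one sample of about 300 children, so its fit is somewhat optimistic and no check in other children is planned

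*Protocol article*

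**What the plan says.** Phase 4, Knowledge holders, recruitment and data collection, names one sample: "A sample of around 300 children will be recruited via partner organisations and through investigator and research team networks". Its size rests on precedent: "This sample size will be sufficient to conduct psychometric analyses, based on our experience and our existing project with youth", and on the adult study, "in which a similar sample size completed a survey with 30 candidate well-being items". The Community involvement section assigns about 300 children to validation and about 400 to preference scoring.

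Phase 4, Statistical analysis, then lists the steps. EFA examines dimensionality "without imposing a pre-specified structure of dimensions". Items that load on no factor may be dropped, weighed against other criteria such as importance in Phase 2. After that, "Confirmatory Factor Analysis will also be used to test the preferred dimension structure", and "A range of statistics will be used to assess model fit and guide dimension development". Item response theory (IRT) also informs which items stay. Invariance and differential item functioning follow under Exploratory testing, with no other sample named.

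The Phase 4 Collaborative analysis section treats the measure as final when the phase ends. Phase 5 gives about 400 children a Best Worst Scaling task of 10–12 paired choices, analysed by multinomial logit. No factor, fit or reliability analysis appears there, and Methodological limitations does not mention the point.

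**The concern.** As described, the same responses suggest the structure, help decide which items survive, and then judge the result. Fit statistics do two jobs, shaping the dimensions and assessing them. Chance features of these 300 children that favour a set of items or factors count in its favour twice, so apparent fit and, to a lesser extent, apparent reliability exceed what new children would show.

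The structure is used downstream. Phase 5 plans factor summative scores and dimension-specific preference scores, and the measure is meant to inform clinical, educational and policy decisions. A reader who sees a passed confirmatory test would credit the structure with more support than one sample can give.

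**Working it through.** **Inputs from the article**
- Phase 4 sample: about 300. No power, precision or target-fit inputs are given, so this figure cannot be reproduced.
- Candidate items: 30 in the earlier projects. The number for this study is not stated, so 30 is an assumption. That gives 300/30 = 10 children per candidate item.
- Final measure: "we anticipate that there will be 16–18 items in the final measure". The simulations aimed for 17.
- Phase 5: 8 blocks × 50 = 400. This reproduces, but it serves the preference model only.

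**Quantities compared**
- CFI = 1 − max(χ² − df, 0) / max(χ₀² − df₀, χ² − df), where the subscript 0 marks the independence model.
- RMSEA = √[max(χ² − df, 0) / (df × (n − 1))].
- Alpha = k/(k − 1) × (1 − sum of item variances / variance of the sum).
- Optimism = value in the 300 children used for selection minus value in a fresh 300, with the structure carried over and the model refitted.

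**Assumed populations (not from the article)**
- A: 30 five-category items, 4 correlated factors, minor misfit; 150 populations per scenario.
- B: 30 continuous items, 5 factors correlated 0.4, main loadings 0.3–0.7, a few small cross-loadings, small minor factors; 300 runs for loading-based selection and 120 for fit-guided selection.

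Both used principal-axis EFA with promax rotation, reduction to about 17 items, and maximum-likelihood CFA. Fit-guided selection in A searched 2–5 factors and two item-ranking rules and kept the best CFI. In B it dropped items one at a time to maximise CFI.

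| Population and selection | CFI, same | CFI, new | Gap | Alpha, same | Alpha, new | Gap |
|---|---|---|---|---|---|---|
| A, one EFA then CFA | 0.921 | 0.913 | 0.008 | – | – | – |
| B, loadings only | 0.895 | 0.885 | 0.010 | 0.601 | 0.580 | 0.021 |
| A, fit-guided | 0.936 | 0.906 | 0.030 | 0.66 | 0.63 | 0.03 |
| B, fit-guided | 0.961 | 0.898 | 0.063 | 0.564 | 0.553 | 0.011 |

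Mean RMSEA in B was 0.051 (same) against 0.053 (new) with loadings only, and 0.026 against 0.046 with fit-guided trimming.

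**Across cut-offs.** Under fit-guided selection, CFI of at least 0.90 was reached in 92% (same) against 61% (new) of runs in A. CFI of at least 0.95 was reached in 74% against 7.5% in B. With loadings only in B, same-sample CFI exceeded new-sample CFI in 59% of runs, so the gap is small beside sampling variation.

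**Can the same-data CFA fail?** Yes. Even with fit-guided selection it missed 0.90 in 100 − 92 = 8% of runs in A and missed 0.95 in 100 − 74 = 26% in B. With loadings only in B, the mean of 0.895 lies below 0.90.

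**Would splitting the 300 solve it?** A 150/150 split leaves 150/30 = 5 children per candidate item for the EFA. In B, with loadings only, mean hold-out CFI was then 0.863, so a split is thin.

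**The case against.** The strongest reply is that the article never says in so many words that the CFA uses the same children as the EFA. It condenses a fuller protocol, and a split or cross-validation could be specified there. This lowers certainty but does not remove the point. The article states a sequence, names one validation sample, presents the last step as a test, and justifies 300 by precedent with no allowance for a hold-out.

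Several other objections stand and limit the point:
- A reader might infer that a CFA on the data that produced the structure cannot refute it. That is wrong: EFA leaves cross-loadings free, CFA normally fixes them at zero, and the simulated models did fail.
- A reader might take the larger gaps as what this plan would produce. The article does not describe a best-CFI search. Selection is also restrained by Phase 2 importance and Co-design Working Group (CWG) review, which the simulations did not model.
- Reliability optimism is small.
- Invariance testing is labelled exploratory and was not simulated, so no size can be claimed for it.
- CWG and Phase 2 judgements cannot be re-run in each bootstrap sample, so resampling corrects only part of the process.
- Extra items for children from age 5 are not free. The article already lists survey feasibility for the youngest as a limitation.

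**Conclusion.** The point holds in a limited form. Followed as written, Phase 4 yields fit that is optimistic and not independently confirmed, and no later phase supplies the check. Under the assumed populations, CFI optimism is about 0.01 with loading-based selection, and about 0.03–0.06 only if fit strongly drives selection. Optimism in alpha is about 0.01–0.03. These sizes depend on 30 candidate items and on factor numbers, loadings and misfit that the article does not give, so they are illustrative. The documents do not support the stronger readings that the CFA is empty or that reliability is badly inflated. This is a worthwhile, inexpensive improvement and not a fatal flaw.

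**What to change.** 1. Describe the Phase 4 CFA as model refinement and not as a test of the structure.
2. Report bootstrap or cross-validated fit and reliability beside the apparent values, repeating the algorithmic steps (EFA, loading and IRT rules, CFA) in each resample. State that CWG and Phase 2 judgements are held fixed, so the correction is partial.
3. If piloting shows the added time is acceptable, have some or all of the roughly 400 Phase 5 children complete the 16–18 item final measure, and check structure and reliability there. A random half would be about 200 children, fewer than the 300 being checked but all new to the structure. No further recruitment is needed. Phase 2 data collection is still under way, so the later phases can be changed.

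Cost: extra analysis, selection rules explicit enough to program, a somewhat longer survey (now about 20 minutes) for the Phase 5 children concerned, and slightly less favourable reported fit.

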#### Exploratory testing

We will conduct exploratory measurement invariance (MI) testing to explore whether the measure functions equivalently across key sociodemographic groups (eg, age, sex, remoteness). This analysis will test whether the measure has the same meaning and structure across these groups, ensuring fair and valid assessment for all Aboriginal and Torres Strait Islander children.

MI will be evaluated hierarchically across two levels. Configural invariance tests whether the same factor structure holds across sociodemographic groups. Scalar invariance tests whether item intercepts are equivalent across groups (ie, children with the same level of well-being respond similarly regardless of sociodemographic characteristics).

Model fit will be assessed using standard fit indices (Comparative Fit Index (CFI), Tucker-Lewis Index, Root Mean Square Error of Approximation (RMSEA), and Standardised Root Mean Square Residual), with changes in CFI ≤0.010 and RMSEA ≤0.015 between nested models indicating invariance.^52 53^ If full scalar invariance is not achieved, partial invariance testing will be conducted to identify any items that function differently across groups.

Additionally, we will examine differential item functioning (DIF) using Item Response Theory methods to identify whether specific items perform differently across sociodemographic groups after controlling for overall well-being levels. Items showing substantial DIF (McFadden’s pseudo R² ≥0.02) will be reviewed with the CWG to determine whether differences reflect meaningful variation or measurement bias requiring item modification.^54^

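### The cut-off for substantial DIF is written as a pseudo R² of at least 0.02, without saying that it is a change between nested models

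*Protocol article*

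**What the plan says.** The DIF analysis is described in the last paragraph of Exploratory testing, under Phase 4 of the protocol article. Its aim is to "identify whether specific items perform differently across sociodemographic groups after controlling for overall well-being levels". The decision rule follows: "Items showing substantial DIF (McFadden’s pseudo R² ≥0.02) will be reviewed with the CWG". The review is "to determine whether differences reflect meaningful variation or measurement bias requiring item modification". The rule does not say change or difference, and it names no models.

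The paragraph before it, on measurement invariance, words its limits differently: "with changes in CFI ≤0.010 and RMSEA ≤0.015 between nested models indicating invariance". There the quantity is plainly a difference between two models.

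Two other places bear on the point. The Phase 4 recruitment section gives the size: "A sample of around 300 children will be recruited via partner organisations". The Phase 4 Statistical analysis section lists DIF among the item response theory results that will help decide which items are kept.

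**The concern.** McFadden's pseudo R² is 1 minus the ratio of a model's log-likelihood to that of a model with intercepts only. It describes total fit. If well-being is in the model, as controlling for it requires, most of the pseudo R² of a sound item comes from well-being. A cut-off on the total then picks out items that measure well-being adequately. It says almost nothing about whether groups answer differently at the same level of well-being.

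The 0.02 is the only numerical DIF criterion in the article, and it decides which items go to the CWG as possibly biased. An analyst who followed it literally would send most of the sound items to review with no means of picking out those with real DIF, while the weakest items would tend to be spared. An analyst who took it as an increment would still have to choose the pair of models. Adding group, adding the interaction, or adding both gives different values against the same 0.02.

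**Working it through.** The 0.02 is a chosen cut-off, so there is no derived figure to reproduce. The check is how the rule behaves under each reading.

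**Inputs from the article.** Sample about 300 (Phase 4 recruitment). Cut-off 0.02 (Exploratory testing). For the final measure, "we anticipate that there will be 16–18 items in the final measure" (Phase 5, Sample size), so the well-being score was built from 16 items other than the one tested.

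**Assumptions not in the article.** Graded-response items with 3, 4 or 5 levels; discrimination 0.3 to 2.5; two groups of 150; a group shift in the item thresholds of 0, 0.5 or 1.0 SD; 60 replicates per cell.

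**Models (ordinal logistic).** M0: intercepts only. M1: well-being score. M3: score + group + score × group.

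- Literal reading: R²(M1) = 1 − lnL(M1)/lnL(M0). Since M1 is nested in M3, R²(M3) cannot be smaller, so using M3 would flag at least as many items.
- Incremental reading: R²(M3) − R²(M1) = [lnL(M3) − lnL(M1)] / [−lnL(M0)].

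**Items with no DIF.** Ranges are over 3, 4 and 5 levels.

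| Discrimination | Mean R²(M1) | Reach 0.02, literal | Mean change | Reach 0.02, change |
|---|---|---|---|---|
| 0.3 | 0.010–0.011 | 12–13% | 0.002–0.003 | 0% |
| 0.5 | 0.022–0.026 | 45–63% | 0.002–0.003 | 0% |
| 0.8 | 0.052–0.064 | 98–100% | 0.002–0.003 | 0% |
| 1.0 | 0.076–0.093 | 100% | 0.002–0.003 | 0% |
| 1.5 | 0.143–0.176 | 100% | 0.002–0.004 | 0% |
| 2.0 | 0.205–0.254 | 100% | 0.002–0.004 | 0–2% |
| 2.5 | 0.259–0.320 | 100% | 0.003 | 0% |

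**Hand check of the change column.** If all K levels are used equally, −lnL(M0) = 300 × ln K, which is 329.6, 415.9 and 482.8 for K = 3, 4 and 5. With no DIF, twice the gain in log-likelihood is roughly chi-squared on 2 degrees of freedom, so the expected gain is about 1. The expected change is 1/329.6 = 0.0030, 1/415.9 = 0.0024 and 1/482.8 = 0.0021, which agrees with the table.

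**Items with real DIF.** On the change, a 1.0 SD shift is flagged in 73–85% of replicates at discrimination 1.0 and in 98–100% at 1.5 and above. A 0.5 SD shift is flagged in 20–32% at 1.5 and 58–68% at 2.0. The literal quantity does not respond in this way: at discrimination 1.5 with 3 levels, mean R²(M1) is 0.176 with no shift and 0.143 with a 1.0 SD shift, and every replicate passes 0.02 in both cases.

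**The case against.** The strongest reply is that nobody would read the rule literally. The parenthesis qualifies DIF, and the sentence before it describes DIF as a group difference with well-being held constant. A model with no group term cannot yield an amount of DIF, so the natural reading is the pseudo R² that group adds. The sentence also carries a citation that is not at hand, and an article may leave the model pair to a fuller document. Most of this stands, and it is why the point is one of wording and not of a wrong method. It does not remove the point. The article chose to state the statistic and the cut-off, and the statistic it names is not a measure of DIF.

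Three stronger readings are tempting, and the documents do not support them.

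- A reader might infer that the rule would flag every item. It would not: weak items often fall below 0.02, as the table shows. Phase 4 tests candidate items before selection, and the earlier projects are said to have used 30, so some weak items are plausible.
- A reader might infer that a flag changes or removes an item. The article says only that it prompts review, in an analysis labelled exploratory. The CWG is consulted before items are finalised in any case.
- A reader might infer that the well-being score must be purified of flagged items. That is a matter of preference, and nothing in the article makes its absence an error.

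A literal application would also be noticed quickly, because nearly all the good items would be flagged at once.

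**Conclusion.** The point holds as a minor misstatement of a decision threshold. Taken literally in a model that controls for well-being, the 0.02 cut-off would be met by practically every adequately discriminating item without DIF: 98–100% at discrimination 0.8 and above, against 0–2% when the cut-off is placed on the change. It would not separate DIF from ordinary discrimination.

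The percentages depend on the assumed response levels, discriminations, equal groups and a score from 16 other items, with 60 replicates per cell. The mid-range figures are therefore approximate: near 50%, the 95% simulation error is about 1.96 × √(0.25/60) = 13 percentage points. The direction does not depend on these choices, because a total-fit statistic includes what well-being explains. The text around the rule suggests that an increment was intended, and the documents do not show that the final measure would be biased.

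**What to change.** Replace the parenthesis with an explicit increment: an item shows substantial DIF if McFadden's pseudo R² increases by at least 0.02 from the model with well-being only to the model that adds group and group × well-being. If the team means a different pair of models, such as group alone, it should name that pair instead. The cost is one sentence. The design, sample, data collection and role of the CWG do not change.
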